## Background

Major depressive disorder (MDD) is the most common psychiatric disease worldwide and represents a leading cause of years lived with disability, resulting in a substantial socio-economic impact [1]. The main goal of treating MDD is to achieve remission and to maintain the therapeutic effects over time. Despite the availability of different classes of antidepressant drugs (ADs), the success of pharmacological treatment is still unsatisfactory, and matching a patient to his/her optimal treatment generally requires multiple trials of different treatments, with the sobering observation that the more treatments that are tried without success, the less likely a successful outcome is. Only approximately one third of patients achieve remission after the first treatment course, while another approximately one third develop treatment-resistant depression (TRD) [2, 3]. The high percentage of treatment failure or incomplete remission could be a consequence of intrinsic biological and environmental heterogeneity among MDD patients [4, 5], suggesting that biomarkers of the response to ADs would be useful for clinicians to guide treatment at the individual level. In this context, pharmacogenomics (PGx) testing has the potential to reduce antidepressant discontinuation due to side effects and increase efficacy.

Recently, assay-guided treatment has shown promising results. Several observational and randomized controlled trials (RCTs) have been conducted to investigate the impact of pharmacogenetics or pharmacogenomics testing on antidepressant outcome in MDD patients with interesting results [6, 7].

This article presents the protocol for the RCT and is written to comply with the recommended SPIRIT guidelines for RCT protocols (Additional file 1).

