## Methods

### Eligibility criteria

Three hundred MDD out-patients are voluntarily enrolling in the study. Patients are referred to psychiatric services (University Department of Mental Health, Spedali Civili Hospital, and IRCCS Istituto Centro San Giovanni di Dio Fatebenefratelli – Brescia, Italy) to receive a new AD due to the failure of their current treatment and/or the onset of adverse effects. The diagnostic inclusion criteria are as follows: a current diagnosis of unipolar depression according to the Diagnostic and Statistical Manual of Mental Disorders-5 (DSM-5) [8] classification system criteria with a Hamilton Depression Rating Scale (HAMD-17) [9] score ≥14, age range 18–65 years, and Caucasian ethnicity. The exclusion criteria are cognitive impairment (Mini Mental State Examination MMSE <24) [10]; neurological disorders; diagnosis of MDD with psychotic features, bipolar I and II disorders, schizophrenia spectrum and other psychotic disorders, obsessive-compulsive disorder, post-traumatic stress disorder, alcohol and substance abuse in the last 3 months; comorbidity with personality disorders (cluster A and/or B); pregnancy; and comorbidity with other severe medical illness. Diagnoses are confirmed using the Italian version of the Structural Clinical Interview for DSM-5 disorders (SCID-5-CV) [11] and the Structural Clinical Interview for personality disorders (SCID-5-PD) [12]. After the enrolment of MDD patients in accordance with the inclusion and exclusion criteria and after obtaining written informed consent, for all patients, DNA is collected through a buccal brush.

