### Randomization and concealment

Eligible patients are randomized to the Treated with Genetic Test Guide (TGTG) group or Treated as Usual (TAU) group. The allocation to the TGTG or TAU group is performed with simple randomization software (http://glimmpse.samplesizeshop.org/) by the project manager who is not involved in either the evaluation or the treatment. The allocation of the patients is communicated directly from the project manager (AM) to the prescriber. None of the other people involved in the projects are informed and/or have access to the allocation information. The randomized allocation sequence of the trial participants is conserved in a double file protected by a double password owned by the PI (MG) and the project manager (AM).

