### Sample size

Based on previous PGx studies performed on MDD patient cohorts [19, 20], the sample size needed to detect a significant reduction in symptom scores was calculated. The analysis revealed that a sample size of 225 participants (⁓112 per group) is required to observe a 15% reduction in symptom scores with a common standard deviation of 45%, alpha = 0.05, and power = 80%. Assuming an estimated drop-out rate of 20–25%, as already observed in follow-up studies on MDD [21], a total sample size of 300 participants will be enrolled in this study.

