### Baseline demographic and clinical features

Age (years) and mean (SD); gender (%F); education (years) and mean (SD); race (%); smokers (%); body mass index (BMI) and mean (SD); age of onset (years) and mean (SD); depression category; moderate, severe, or very severe (%); recurrence (%); presence of psychotic symptoms (%); comorbidity with personality disorders congruent with inclusion/exclusion criteria (%); comorbidity with anxiety disorders (%); presence of psychiatric disorders among the first-degree relatives (%); HAMD-17 at baseline and mean (SD); BDI-II at baseline and mean (SD); BAI-II at baseline and mean (SD); mini-ICF-APP at baseline and mean (SD); MMSE at baseline and mean (SD); UKU at baseline and mean (SD); previous failed adequate treatment; CECA-Q mother antipathy (hostility, coldness) (%); CECA-Q father antipathy (hostility, coldness) (%); CECA-Q mother neglect (%); CECA-Q father neglect (%); CECA-Q physical abuse mother (%); CECA-Q physical abuse father (%); CECA-Q sexual abuse (%); and Paykel score and means (SD).

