### Statistical analysis

Analysis of variance (ANOVA) or the Kruskal–Wallis and Mann–Whitney *U* nonparametric tests and the chi-squared test will be used to analyze differences in continuous and categorical variables, respectively, between groups. Pearson’s correlation analysis will be used to evaluate bivariate correlations. Parametric and nonparametric tests will be used to meet relative assumptions (i.e., distribution, sample size).

To pursue our primary outcome, the analyses will be performed for patients who complete the study through week 8. The analysis will be performed using mixed-effects models with repeated measures (MMRM) to examine the effect of time and group (TGTG vs. TAU) on the reduction in the HAMD-17 score. The model includes the fixed effect continuous factor baseline HAMD-17 and fixed effect categorical factors, which are the treatment group (TGTG and TAU; 2 levels), visit (weeks 4 and 8; 2 levels), and treatment x visit interaction. The mean changes in the HAMD-17 at week 8 in the TGTG and TAU groups will be estimated and tested utilizing the LS means from the treatment x visit interaction in the MMRM model. The primary analysis will test the difference (contrast) between the week 8 least squares (LS) means at a two-sided significance of 0.05. To achieve the secondary outcome, the generalized linear mixed model will be used for response and remission analyses. The analyses of the tertiary outcomes will be performed for exploratory purposes with the same statistical models. Comparisons between the TGTG and TAU means at all timepoints of evaluation will also be performed for descriptive purposes. Finally, an intention-to-treat (ITT) analysis will be performed for all the patients who undergo at least one post-treatment assessment for efficacy during the study. The last observation will be carried forward on the HAMD-17. All the statistical analyses will be performed using R Statistical Software (R Foundation for Statistical Computing, Vienna, Austria).

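### The primary model omits previous failed treatment, a baseline item the article collects and links to outcome: a modest, recoverable loss of precision

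*Protocol article*

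**What the plan says.** The relevant statements are spread over several sections of the protocol article.

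- **Statistical analysis:** the primary model is written out term by term. "The model includes the fixed effect continuous factor baseline HAMD-17 and fixed effect categorical factors, which are the treatment group", with visit (weeks 4 and 8) and treatment by visit completing the list. The test is then fixed: "The primary analysis will test the difference (contrast) between the week 8 least squares (LS) means at a two-sided significance of 0.05".
- **Randomization and concealment:** "The allocation to the TGTG or TAU group is performed with simple randomization software". No stratum, block or minimisation factor is named.
- **Background:** on successive antidepressant treatments, "the more treatments that are tried without success, the less likely a successful outcome is".
- **Eligibility criteria:** patients are referred "to receive a new AD due to the failure of their current treatment and/or the onset of adverse effects".
- **Baseline demographic and clinical features:** the items to be described include "previous failed adequate treatment". The article does not say whether this is a count or a yes/no item.

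No section uses the failure history in the allocation or in the primary model.

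**The concern.** The article gives its own reason to expect treatment history to predict outcome, and it collects that history before treatment starts. Entry is for failure, adverse effects or both, so the history should differ between patients. Simple randomisation does not force it to be equal in the two arms, and the model does not adjust for it.

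Two things follow. Outcome variation that could be explained stays in the error term and widens the confidence interval. If, by chance, one arm has more patients with several past failures, the estimated difference shifts and nothing in the primary model corrects it. Because the article states the covariates explicitly, this is a choice already made, not a detail left to a later analysis plan.

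**Working it through.** **Inputs.** From Sample size: "a 15% reduction in symptom scores with a common standard deviation of 45%, alpha = 0.05, and power = 80"%, 225 analysed (about 112 per arm), 300 enrolled. From Statistical analysis: a two-sided 0.05 test. The week 8 contrast is approximated by a comparison of two means with 112.5 per arm, and 45 is taken as the residual SD before failure history is added.

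**1. The plan's own figure.** n per arm = 2 × (SD/difference)² × (z_alpha + z_beta)² = 2 × (45/15)² × (z_alpha + 0.842)².

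- One-sided 0.05: 18 × (1.645 + 0.842)² gives 112 per arm, 224 in total, which matches 225.
- Two-sided 0.05: 18 × (1.960 + 0.842)² gives 142 per arm, 284 in total, which does not.

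So 225 reproduces only with a one-sided alpha. That mismatch is a separate point. It matters here only because it sets the starting power for the two-sided test the plan specifies.

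**2. Power with no further covariate.** (15/45) × √(112.5/2) = 2.50, and Φ(2.50 − 1.96) = Φ(0.54) = 70.5%.

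**3. Power with failure history in the model.** If it explains a share R² of the residual variance, the SD becomes 45 × √(1 − R²) and power is Φ(2.50/√(1 − R²) − 1.96). The article gives no R², so a range is assumed.

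| Assumed R² | Residual SD | Two-sided power at 225 | Total needed for 80% |
|---|---|---|---|
| 0 | 45.0 | 70.5% | 284 |
| 2% | 44.6 | 71.4% | 278 |
| 5% | 43.9 | 72.7% | 270 |
| 10% | 42.7 | 75.0% | 256 |

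Put as patients: 225/0.98 is about 230 and 225/0.90 = 250, so adjustment is worth roughly 5 to 25 additional analysed patients.

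**4. Chance imbalance.** Treat failure history as a binary factor (for example, several past failures or not) with an assumed prevalence p. With equal arms, the SE of the difference in prevalence is √(4p(1 − p)/N). At N = 225:

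- p = 30%: SE 6.1 percentage points, 95% range ±12.0, probability of an imbalance above 10 points 10%.
- p = 50%: SE 6.7 percentage points, 95% range ±13.1, probability of an imbalance above 10 points 13%.

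**5. What such an imbalance does.** A binary factor that explains R² of the variance has an effect of 45 × √R² / √(p(1 − p)). At p = 50%, this is 12.7 points for R² = 2% and 28.5 points for R² = 10%. A 10-point imbalance then moves the unadjusted difference by 1.3 to 2.8 points, against a target of 15.

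**The case against.** The strongest reply is that nothing here is an error. Allocation has no strata, so no stratification factor is missing from the model. The model adjusts for baseline severity and is prespecified. The Background sentence is a general remark about successive treatments; it does not show that failure history predicts percent change in HAMD-17 in this cohort once baseline score is accounted for. The cohort is already selected for failure or intolerance, which may narrow the range of histories. The gain rests entirely on an assumed R², and at 2% to 5% it is only about 1 to 2 percentage points of power.

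Most of this stands, and it limits the point to a modest improvement. It does not remove it, because the covariate is already collected, the article itself gives the reason to expect it to matter, and adjusting costs almost nothing.

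A reader might infer more than the documents support:

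- **That the omission biases the primary comparison.** It does not: randomisation protects the unadjusted comparison of those randomised, and the type I error is valid. Restricting the primary analysis to patients who complete week 8 is a different matter, which this covariate would not cure.
- **That simple randomisation is itself a defect.** With 300 patients, arm sizes differ by 20 or more in 27% of trials, but the consequence is trivial. A 140/160 split with 25% drop-out leaves 105/120, with power of 70.3% against 70.5% for equal arms. Covariate adjustment would not change arm sizes either.
- **That recruiting service belongs in the same argument.** It is not among the listed baseline features. The Discussion mentions local service organisation only as a limit on generalisability, and no section calls it prognostic for the comparison.
- **That adjustment would restore 80% power.** Even an R² of 20%, a partial correlation of about 0.45 (√0.20) for which the article offers no evidence, gives 79.8%.

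**Conclusion.** The point holds as a precision issue. The primary model leaves out a baseline variable that the article collects and whose relevance it asserts, and the allocation method does not balance that variable.

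The planned test is valid without it. On the plan's own difference and SD, with 225 analysed and the stated two-sided test, the forgone gain is about 1 to 4.5 percentage points of power (70.5% to between 71.4% and 75.0%). A chance imbalance in failure history above 10 percentage points, with a probability of about 10% to 13%, would go uncorrected.

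These figures depend on an assumed 2% to 10% of residual variance explained and an assumed prevalence of 30% to 50%; the shift of 1.3 to 2.8 points uses the 50% prevalence. The article supplies none of these values. The low base of 70.5% comes from the separate one-sided/two-sided discrepancy and should not be counted as part of this point.

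**What to change.** Before outcomes are examined by arm, prespecify previous failed adequate treatment as a fixed effect in the primary MMRM and in the generalised linear mixed models for response and remission. Use the form in which it is recorded, and state that form: a count or a yes/no item costs one degree of freedom, and a categorical item costs one fewer than its number of categories. Keep baseline HAMD-17 and the other terms as they are.

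No new data, visits or patients are needed. Trial status describes recruitment as still under way, so the change could be made in advance at the date of the article; made after the results are known, the same change would look data-driven.

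Recruiting service may be added as a further fixed effect, taken from the enrolment site, but this is optional. Leave randomisation unchanged.

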### Outcomes

The primary outcome is symptom improvement at week 8, as measured by the percent change in the HAMD-17 score from baseline, between the two groups.

Secondary outcomes include response and remission rates at 4, 8, and 12 weeks according to the HAMD-17.

Tertiary outcomes include (1) changes in scores of depressive symptoms at 4, 8, and 12 weeks compared with baseline according to the BDI-II; (2) response and remission rate at 4, 8, and 12 weeks according to BDI-II; (3) changes in scores of anxiety symptoms at 4, 8, and 12 weeks compared with baseline as measured by the BAI; (4) changes in scores of psychosocial functioning at 8 and 12 weeks compared with baseline as measured by the MINI-ICF-APP; and (5) side effects at 4, 8, and 12 weeks as assessed by the UKU Side Effect Rating Scale.

The response is defined as a ≥50% decrease in the assessment of interest (HAMD-17, BDI-II) at weeks 4, 8, and 12 compared with the baseline. Remission is defined as a score of ≤7 for HAMD-17 and ≤9 for BDI-II.

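### The primary MMRM lists baseline HAMD-17 only as a main effect, so weeks 4 and 8 share one slope and the week-8 contrast can lose a little precision

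*Protocol article*

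**What the plan says.** The Statistical analysis section of the protocol article states the primary model term by term: "The model includes the fixed effect continuous factor baseline HAMD-17 and fixed effect categorical factors", the latter being treatment group, "visit (weeks 4 and 8; 2 levels), and treatment x visit interaction". Treatment may act differently at the two visits, but baseline may not. One comparison is confirmatory: "The primary analysis will test the difference (contrast) between the week 8 least squares (LS) means at a two-sided significance of 0.05". On the analysis set it says that "the analyses will be performed for patients who complete the study through week 8".

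The Outcomes section defines the primary outcome "as measured by the percent change in the HAMD-17 score from baseline". The Statistical analysis section speaks instead of reduction and mean change in the score, so the modelled scale is not settled beyond doubt. The article gives no covariance structure, no SD by visit and no correlation of baseline with later scores.

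**The concern.** A baseline main effect in a repeated-measures model imposes one regression slope on every visit. If baseline relates differently to the week-4 and week-8 scores, the shared slope is a weighted average of the two. It is then not the best slope for week 8, the only visit that is tested. Some variance that baseline could explain at week 8 stays in the contrast. A baseline by visit term removes the constraint: in patients with both visits and with unstructured covariance, the week-8 estimate becomes the ordinary week-8 ANCOVA. At stake is a small amount of precision, not the validity of the test.

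**Working it through.** **The plan's own figure.** The Sample size section plans for "a 15% reduction in symptom scores with a common standard deviation of 45%, alpha = 0.05, and power = 80" per cent. With n per arm = 2 × 45² × (z_alpha + z_power)² / 15² = 18 × (z_alpha + z_power)²:
- one-sided 0.05: 18 × (1.645 + 0.842)² = 111.3, so 112 per arm, which matches the stated 225 in total;
- two-sided 0.05: 18 × (1.960 + 0.842)² = 141.3, so 142 per arm.

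The inflation 225 / (1 − 0.25) = 300 also reproduces. The mismatch in sidedness is a separate matter. What counts here is that the calculation uses no baseline adjustment, so a change in the baseline term alters no stated figure.

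**Formulae** (both visits observed, unstructured covariance, large samples). Let sx be the baseline SD, s4 and s8 the SDs at weeks 4 and 8, r4 and r8 their correlations with baseline, and rho the between-visit correlation.
- Slopes: β4 = r4·s4/sx and β8 = r8·s8/sx.
- Residual terms: S44 = s4²(1 − r4²), S88 = s8²(1 − r8²), S48 = s4·s8(rho − r4·r8).
- Weight of week 4 in the shared slope: w4 = (S88 − S48)/(S44 + S88 − 2·S48).
- Shared slope: b = w4·β4 + (1 − w4)·β8.
- Variance ratio at week 8, shared over visit-specific slopes: 1 + (β8 − b)²·sx²/S88. It is never below 1.

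Score and change in score give the same answer, because taking the change lowers both slopes by 1.

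**Score scale.** All inputs are assumed: sx = 4.5, s4 = 6, s8 = 7.

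Worked case, r4 = 0.6, r8 = 0.3, rho = 0.6:
- S44 = 36 × 0.64 = 23.04; S88 = 49 × 0.91 = 44.59; S48 = 42 × (0.6 − 0.18) = 17.64.
- w4 = 26.95/32.35 = 0.833.
- b = 0.833 × 0.800 + 0.167 × 0.467 = 0.744.
- Ratio = 1 + (0.467 − 0.744)² × 20.25/44.59 = 1.035.

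| r4 / r8 | rho | β4 | β8 | w4 | b | ratio |
|---|---|---|---|---|---|---|
| 0.60 / 0.514 | 0.7 | 0.800 | 0.800 | 0.75 | 0.800 | 1.000 |
| 0.6 / 0.4 | 0.7 | 0.800 | 0.622 | 0.85 | 0.774 | 1.011 |
| 0.5 / 0.3 | 0.7 | 0.667 | 0.467 | 0.85 | 0.636 | 1.013 |
| 0.6 / 0.3 | 0.6 | 0.800 | 0.467 | 0.83 | 0.744 | 1.035 |
| 0.6 / 0.3 | 0.7 | 0.800 | 0.467 | 0.95 | 0.783 | 1.046 |

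**Simulation check.** With 112 per arm, 3000 trials per case and other assumed inputs (baseline SD 4), the ratio was 0.999 with equal slopes, 1.004 for correlations 0.5/0.35 and 1.038 for 0.6/0.3. The week-4 weights were 0.50, 0.745 and 0.895. The mean error of the contrast was at most 0.023 points and practically the same for both models, so there is no bias.

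**Percent-change scale.** The slope of percent change on baseline is roughly 100(β − m/m0)/m0, where m is the mean score at the visit and m0 the baseline mean. The slopes at the two visits therefore differ by 100[(β4 − β8) − (m4 − m8)/m0]/m0. If patients keep improving from week 4 to week 8, the second term offsets the first. With the same assumed SDs and correlations, the large-sample ratios were 1.0005 to 1.010, and a simulation gave 0.9988.

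**In patients and power.** An inflation of 1% is worth 225 × (1 − 1/1.01) ≈ 2 patients; 4% is worth 225 × (1 − 1/1.04) ≈ 9. At 112 per arm, a 15-point difference and residual SD 45, two-sided power is 70.3%. With 1% more variance it is 69.9%.

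**The case against.** Four points can fairly be made against raising this.

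- **It is not a mistake.** A prespecified MMRM with baseline as a main effect is valid, and randomisation keeps the contrast unbiased. This stands. The limited reply is conditional: given a chance baseline imbalance of two standard errors, 2 × 4.5 × √(2/112) = 1.20 points, the worked case shifts the contrast by (0.744 − 0.467) × 1.20 = 0.33 points. That is 0.37 of its standard error, √(44.59 × 2/112) = 0.89. Over repeated randomisations such shifts average out; they are the lost precision seen from another side.
- **On the declared outcome the loss is close to nil.** This also stands. The larger figures apply only if the score itself, or its change, is modelled.
- **A weaker correlation at week 8 does not mean a different slope.** This is right: with SDs of 6 and 7, a fall from 0.60 to 0.514 leaves the slopes equal and nothing is lost. The range must start at zero.
- **The article condenses a longer protocol, which may contain the term.** That is possible, but the article spells out the model's terms, and this one is not among them.

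A reader might go further and infer that the shared slope is mostly set by week 4, that it over-adjusts at week 8, or that precision is certainly lost. The documents support none of these. The weight depends on SDs, correlations and a covariance structure that the article does not give. It is 0.50 with equal variances and correlations, and across the inputs tried it ran from 0.34 to above 0.9.

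**Conclusion.** The point holds as a minor, optional refinement. The listed terms do tie baseline to one slope over both visits, and in large samples freeing it cannot reduce week-8 precision. Under the assumed inputs (SDs 4.5, 6 and 7; correlations falling by 0 to 0.3; unstructured covariance; both visits observed), the variance inflation is 0% to about 4% on the score scale and about 0 to 1% on the percent-change scale. Inflations of 7 to 13% appeared only when the baseline relation was assumed to change sharply between two visits four weeks apart, and nothing in the article suggests that. The primary test stays valid with or without the change.

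**What to change.** Add baseline HAMD-17 by visit to the fixed effects of the primary MMRM, and record this before analysis. The cost is one model term and one degree of freedom. The week-8 contrast, the significance level, the sample size and every other stated figure stay as they are.

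### The HAMD-17 analysis labelled ITT carries the week-4 score forward in a modified ITT set, so it is a poor check on the completers result

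*Protocol article*

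**What the plan says.** All of the relevant analysis text is in the protocol article, Statistical analysis.

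- **Primary set:** "the analyses will be performed for patients who complete the study through week 8".
- **Primary model:** an MMRM with baseline HAMD-17, group, "visit (weeks 4 and 8; 2 levels), and treatment x visit interaction". The test is the contrast between the week-8 "least squares (LS) means at a two-sided significance of 0.05".
- **Additional set:** "an intention-to-treat (ITT) analysis will be performed for all the patients who undergo at least one post-treatment assessment for efficacy during the study".
- **Missing scores in that set:** "The last observation will be carried forward on the HAMD-17".

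Four other sections bear on the point. Assessments places the ratings at baseline and weeks 4, 8 and 12. Sample size expects 20–25% drop-out among 300 enrolled. The intervention procedure section removes patients who come to need combination or augmentation with antipsychotics or mood stabilizers. Blinding states that prescribers know the allocation.

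**The concern.** A completers analysis needs a companion that shows whether its result survives drop-out. For the HAMD-17, the LOCF analysis is the only one described that could do this, and it has two weaknesses.

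First, the set is not the one its label names. The first follow-up rating is at week 4, so a randomised patient lost before then does not appear.

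Second, a patient who leaves between weeks 4 and 8 is given the week-4 score as the week-8 result. If scores are still falling, that patient is held at a worse value than continued follow-up would have shown. The arm that loses more patients is then marked down, whatever its treatment did.

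Unequal loss is plausible here. Removal for augmentation ties withdrawal to poor response, prescribers are unblinded, and the Background section suggests that testing may reduce discontinuation for side effects. If TAU loses more patients, LOCF favours TGTG; if TGTG loses more, it penalises TGTG. A reader could not tell whether agreement between the two analyses was reassurance or coincidence.

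**Working it through.** **The plan's own figures.** Inputs from Sample size: difference 15, SD 45, power 80%, alpha 0.05.

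- Per group, n = 2 × (z_alpha + z_power)² × (45/15)².
- One-sided: 2 × (1.645 + 0.842)² × 9 = 111.3, so 112 per group. This reproduces the stated total of about 225.
- Two-sided: 2 × (1.960 + 0.842)² × 9 = 141.3, so 142 per group. This does not reproduce it. The mismatch with the two-sided test is a separate matter and is not used below.
- Drop-out: 225 / 0.75 = 300, as stated.

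**How many patients are affected.** If 20–25% are lost by week 8, that is 0.20 × 300 = 60 to 0.25 × 300 = 75 patients. If 30% of them leave before week 4 (assumption), 18 to 23 drop out of the set altogether and about 42 to 52 have a week-4 score carried forward.

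**What LOCF estimates.** Let an arm have loss d by week 8, a fraction f of it before week 4, and mean percent improvements m4 and m8. With random loss:

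- carried share of the set: p = d(1 − f) / (1 − d·f)
- LOCF week-8 mean: m8 − p(m8 − m4)

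Assumptions, none of them in the protocol: TAU improves 25% then 35%. With a true effect of 15, TGTG improves 32.5% then 50%, so half the effect is present at week 4.

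| Loss d | p at f = 0 | p at f = 0.3 |
|---|---|---|
| 15% | 0.150 | 0.110 |
| 22.5% | 0.225 | 0.169 |
| 30% | 0.300 | 0.231 |
| 35% | 0.350 | 0.274 |

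- **No effect, equal loss:** p is the same in both arms, so the bias is 0.
- **No effect, 15% vs 30%:** (0.300 − 0.150) × 10 = 1.5 at f = 0; (0.231 − 0.110) × 10 = 1.2 at f = 0.3. Both favour the better-retained arm.
- **True 15, equal 22.5%:** the week-4 to week-8 gain is 17.5 in TGTG and 10 in TAU. So 15 − 0.225 × 7.5 = 13.3 at f = 0; 15 − 0.169 × 7.5 = 13.7 at f = 0.3.
- **True 15, TGTG loses 35%, TAU 15%:** (50 − 0.350 × 17.5) − (35 − 0.150 × 10) = 43.9 − 33.5 = 10.4 at f = 0; 11.3 at f = 0.3.
- **True 15, TAU loses 35%, TGTG 15%:** (50 − 0.150 × 17.5) − (35 − 0.350 × 10) = 47.4 − 31.5 = 15.9 at f = 0; 15.8 at f = 0.3.

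**Simulation, adding loss driven by a poor week-4 response.** Same means, 150 per arm, correlation 0.6, week-4 SD 35–45, week-8 SD 45, f from 0 to 0.3.

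| Scenario | True | LOCF | All-visits MAR analysis |
|---|---|---|---|
| 15% vs 30% loss | 0 | 1.2 to 2.6, favouring the better-retained arm | about 0 |
| Equal 22.5% loss | 15 | 13.2 to 13.9 | about 15 |
| 15% vs 35% loss, either arm | 15 | 8.7 to 17.4 | about 15 |

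A second simulation assumed a steeper course (20% then 35%) and 15% vs 35% loss. At no effect it gave an LOCF bias of −2.8 to +2.5 with 7.4–8.4% rejection. At a true 15, LOCF coverage was as low as 86%.

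**Standard error.** LOCF's model standard error was about 5.0–5.6 against an empirical SD of 4.9–5.6, so it is right for the quantity LOCF estimates. At 25% random loss it was 5.22, against 5.79 for the likelihood-based analysis and 5.18 for complete data on all 300.

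**The case against.** The case on the other side has several parts.

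- **The effect is modest.** A bias of 1.2 to 2.6 points is 0.03 to 0.06 of the SD of 45, and a quarter to a half of a standard error of about 5.2. It needs one arm to lose twice as many patients, and the protocol gives no split by arm or by timing. This stands, and the sizes are illustrations only.
- **LOCF is not always biased.** With equal loss it has no bias at no effect, and it shrinks a true effect towards zero. This stands too.
- **The comparator is favoured.** The MAR analysis is unbiased here because the data were generated that way. This is correct. Withdrawal for augmentation and unblinded prescribers make MAR uncertain, and an MMRM would then be biased as well.
- **An MMRM shares one defect.** With baseline as a covariate, a patient with no post-baseline rating contributes no outcome and is omitted. Only imputation brings that patient back.
- **The role of the analysis is inferred.** The protocol does not call it a check on drop-out. It is, however, the only stated HAMD-17 analysis that readmits non-completers to the week-8 comparison of scores.

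A reader might also infer three stronger things that the documents do not support. One is that LOCF's standard errors are too small; they match its own sampling variation and are smaller only than those of an analysis that reflects the lost week-8 data. Another is that this is the plan's only analysis of all patients. It does not cover all patients, and the completer restriction is stated for the primary outcome, not for the response and remission models. The third is that missing sensitivity analyses are a fault; those are commonly left to a statistical analysis plan, which is not shown. The point rests only on the stated LOCF and the stated set.

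**Conclusion.** The point holds as a recommended change to a supporting analysis, not as a flaw in the primary test. The label ITT is wrong for the set described, which follows from the text alone. LOCF is a poor choice for the week-8 endpoint because the direction of its error is unknown in advance, so it can be called neither conservative nor a robustness check.

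Rounded, the size is about 1 to 3 points at no effect with 15% vs 30% loss, 13 to 14 for a true 15 with equal 22.5% loss, and 9 to 17 for a true 15 with 15% vs 35% loss. These ranges depend on the assumed trajectories, correlation, drop-out timing and MAR loss. The two structural facts, the carried week-4 value and the excluded early leavers, do not.

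**What to change.** 1. Delete the LOCF sentence.
2. Run this analysis as the MMRM already specified (baseline, group, visit, group by visit) on all randomised patients, as allocated, with at least one post-baseline HAMD-17, using every observed visit. It is valid under MAR.
3. Name that set modified ITT.
4. Add a multiple imputation, referenced to TAU or with a delta adjustment, that covers all randomised patients, including those with no follow-up rating. This step restores the early leavers and tests the MAR assumption.

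The cost is a wording change, a little more work in R, and an interval slightly wider than LOCF would give. No visit or patient burden is added. Make the change together with any revision of the completers-only primary set, since the same all-visits MMRM serves both.
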